### **Objective and Overview of the Study**

to conduct a pilot study to improve insulin sensitivity, prevent weight gain and reduce visceral adiposity in African-American, Hispanic, South Asian, and other high risk populations of normoglycemic, hyperinsulinemic women with midlife weight gain. Enhance the Metabolic Profile of Women with Insulin Resistance (EMPOWIR) will compare three treatment protocols in a randomized, double-blind, clinical trial and optional, post-treatment surveillance analysis.

The objective of the study is to compare the effect of carbohydrate modified diet alone and in combination with metformin (MF) and Avandamet® (metformin plus rosiglitazone (RSG)) on insulin parameters in a wide range of ethnically and economically diverse non-diabetic women (aged 35-55) who meet study selection criteria seen at three academic medical centers: The Hispanic Center of Excellence and The Menopause Research and Treatment Center at Albert Einstein College of Medicine/Montefiore Hospital; The Diabetes Center of Excellence at The University of Tennessee; and The Center for Diabetes and Endocrine Care at New York Medical College/Westchester Medical Center and their affiliated practices. All women will receive the calorie-reduced, carbohydrate modified (sugar restricted, low glycemic index) diet based on large servings of vegetables, fruits, lowfat proteins and dairy products and limited refined carbohydrates and treats. Devised 30 years ago and field-tested in more than a thousand patients in the past decade, this dietary program integrates scientific findings and recommendations from numerous current research studies.

A 3-arm trial will be conducted in a final study population of 75 normoglycemic hyperinsulinemic women (glucose-mediated AUC-insulin >100mU/ml) randomized (Phase 1) to an initial 6-month treatment of study diet, with placebo, metformin, or Avandamet®. Subjects initially randomized to placebo arm will be reassigned after 6 months to one of the two active treatment arms (Phase 2).

Initial funding will be used to develop a core program to facilitate additional research at

[figure not shown]

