| 
Study Design
          | 
Overview
<small>Please see attached Study Flow Chart</small>
 
Chart review of patients at the 3 study Centers and their affiliated General Medical and Gynecology practices and public announcements will be used to identify non-diabetic women who meet selection criteria who will be invited to participate in the study. After obtaining consent, and additional screening for suitability, 80 patients will undergo glucose tolerance testing and additional tests to determine if they meet study inclusion and exclusion criteria. Following a 1-month lead-in phase, an initial study population of 75 women from 3 clinical sites will be randomized to placebo (diet and lifestyle modification) or one of two active study treatment arms for a 6-month study (Phase 1); patients in the diet plus placebo group will then be crossed over to one of the two active study arms for a 2nd six months (Phase 2).
 |
| 
Inclusion / Exclusion
 | 
Inclusion Criteria
 
 
1. Healthy, non-diabetic women with "≥20 pound weight gain since their twenties"
 
2. Age: 35-55
 
3. Peri-menopausal ( FSH ≥25 on day 2-3 of cycle) or postmenopausal status
 
4. Body Mass Index (BMI) 25-35 kg/m^2
 
5. Either:             
 
(a). a single blood pressure recording ≥135/85 or the use of blood pressure medication
 
OR
 
(b) HDL≤50mg/dl or triglycerides ≥150 mg/dl or the use of lipid modifying medication
 
 
 
7. Area-under-the-curve (AUC-)insulin level ≥100μU/ml along with normal fasting (≤100 mg/dl) & postprandial (≤200 mg/dl) glucose determinations following a 75-gram standard oral glucose tolerance test.
 
 
Exclusion Criteria
                                                             |

[figure not shown]

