| Study Endpoints/
Objectives                    | 
The study objective is to compare the effects of metformin, and Avandamet® on markers of insulin resistance – fasting, peak (1-hour) and AUC-insulin, and HOMA-R, and body fat distribution in hyperinsulinemic, peri- and post-menopausal women with progressive weight gain (Syndrome W) prior to the onset of overt glycemic abnormalities or full-blown Metabolic Syndrome.
 
The primary outcome variables will be 1-year change in fasting and 1-hour insulin (as noted below.)
                                                                                                                                                                                                                                                                                                                                                                                                                                                                                                                                              |

|                                                                                |                                                                                                                                                                                                                                                                                                                                                                                                                                                       |
|--------------------------------------------------------------------------------|-------------------------------------------------------------------------------------------------------------------------------------------------------------------------------------------------------------------------------------------------------------------------------------------------------------------------------------------------------------------------------------------------------------------------------------------------------|

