| Outcome Parameters / Analytical Endpoints | 
The primary outcome variables are change from baseline in fasting and one-hour insulin at 1 year. Secondary outcome measures are 6 and 12 month change from baseline in body weight, CT scan-determined visceral adipose tissue other fat compartments, and relevant ratio's; total and multimeric adiponectin; and other cardiovascular risk and inflammatory markers, including lipids, c-reactive protein, TNF-<math>\alpha</math>, leptin, ghrelin, and resistin; and IGF-1 and IGF-binding proteins.
                                                                                                                                                                                                                                                                                                                                                                                                                                                                                                                                                                                                                        |
| Statistical Analysis Plan                 | 
Power Calculations and Assumptions
 
Three power calculations were performed incorporating the significance levels and sample size of TZD-based interventions in recently reported studies and comparator trials. A initial sample size of 25 per group is a realistic estimate and is based on the following assumptions:
 
 
1. Placebo treatment even with intensive dietary intervention (which will not be provided after the lead-in phase of EMPOWIR) has low rates of weight loss and high drop out rates at 6 and 12 months of study follow-up in the majority of published studies
 
2. data from observational and population based studies show annual weight gain in women in the study age range and BMI category
 
3. Metformin has a large treatment effect in hyperinsulinemic women and, in combination with hypocaloric carbohydrate modified diet, reduced fasting insulin by 25-40% and 1-hour (peak) insulin by 50% in our preliminary data. (with a mean body weight change 12.5% at 1-year).
 
4. Enrollment goals assume 10% drop out during Phase 2
 
 |

[figure not shown]

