#### Summary of sample size calculations:

The study design comprises 3 groups in one pre-treatment (Phase 1) and one post-treatment (Phase 3) measurement of outcome. Preliminary data from our open label use of metformin and other randomized clinical trials suggest that metformin affords large treatment effects. Nonetheless, as the large effect may be due in part to placebo, we will structure our sample size to detect more moderate treatment effects. Using an analysis of covariance, a sample size of 60 patients (20 per group) will provide at least 80% power to detect a moderate to large effect size ( $f=.38$ ) for a two-sided test of significance at a critical value of .05. While 20 patients per group are required to meet the anticipated effects, we will target 25 per group to allow for 20% attrition. The proposed attrition rate is less than rates reported in research studies of other medications evaluated for weight reduction, such as sibutramine (32%) and xenical (24%). However, the rate reflects attrition rates from our own preliminary data and from other published studies of patients treated with metformin analyzed using an intention-to-treat or comparable analysis such as studies of obesity in women, and children, PCOS, and HIV-related lipodystrophy.

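### The primary insulin outcomes are read at 1 year, six months after every placebo woman has moved to active drug, so the three-group primary comparison has no diet-alone control

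*Protocol*

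**What the plan says.** **Time point.** Two rows of the protocol table fix it. Under Study Endpoints/Objectives the primary outcome variables "will be 1-year change in fasting and 1-hour insulin (as noted below". Under Outcome Parameters / Analytical Endpoints they "are change from baseline in fasting and one-hour insulin at 1 year".

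**Placebo arm.** Objective and Overview of the Study states: "Subjects initially randomized to placebo arm will be reassigned after 6 months to one of the two active treatment arms (Phase 2". The Study Design row says the same. Neither keeps a subset on placebo.

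**Objective.** Objective and Overview of the Study sets out to "compare the effect of carbohydrate modified diet alone and in combination with metformin (MF) and Avandamet". Study Endpoints/Objectives words it more narrowly, as metformin compared with Avandamet.

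**Sample size.** Summary of sample size calculations states: "The study design comprises 3 groups in one pre-treatment (Phase 1) and one post-treatment (Phase 3) measurement of outcome". By analysis of covariance, "a sample size of 60 patients (20 per group) will provide at least 80% power" at f=.38, "for a two-sided test of significance at a critical value of .05".

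**6-month data.** Study Variables schedules glucose tolerance tests and insulin curves at baseline, 6 and 12 months. Statistical Plan foresees group comparisons of change at both 6 and 12 months. The secondary outcomes, also at 6 and 12 months, cover weight, fat compartments, adiponectin and other risk markers, but neither fasting nor 1-hour insulin.

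**The concern.** A comparison of drug with diet alone needs women who are still on diet alone when the outcome is read. Here that holds at month 6 and not at month 12, and the primary outcome is at month 12.

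At 1 year the group randomised to placebo has had about six months of one drug or the other. Setting it against the active arms estimates early against delayed start, blended over two drugs. A null three-group result could then be read as a failure of the drugs when it may only show that the late starters caught up. The placebo-controlled insulin comparison that the trial does make, at month 6, has no rank among the outcomes, so it would carry little weight whatever it showed.

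**Working it through.** **1. Who is on what.** I read the two active arms as staying on their drug to month 12, which the text implies.

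| Randomised to | Months 0–6 | Months 6–12 |
|---|---|---|
| Diet + placebo | no active drug | metformin or Avandamet |
| Diet + metformin | metformin | metformin |
| Diet + Avandamet | Avandamet | Avandamet |

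Planned number on diet plus placebo at month 12: zero. This settles the main point without arithmetic. Last observation carried forward does not restore the control: it would keep a 6-month placebo value only for women lost before the 12-month test, a selected subset.

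**2. The plan's own figures.** Inputs from Summary of sample size calculations: 3 groups, N=60, f=.38, alpha .05, 20% attrition.

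- Attrition: 20/0.8 = 25 per group and 60/0.8 = 75 in all, as stated.
- Power: noncentral F with 2 and 60−3−1 = 56 degrees of freedom and λ = N·f²/(1−r²), where r is the baseline–outcome correlation. The protocol gives no r.
 - r=0: λ = 60 × .1444 = 8.66; power 73%.
 - r=.385: λ = 8.66/(1−.148) = 10.17; power 80%.

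The stated 80% is therefore reachable with a moderate correlation. Both values of r are carried forward so that each diluted figure has its own reference.

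**3. Dilution with equal active arms.** Put the placebo mean at 0 and both active means at d (SD units). Then f = d·√2/3, so f=.38 gives d=.806. Let switched women show a fraction q of the active effect by month 12. Then f = (1−q) × .38. The documents give no q.

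| q | f at month 12 | Power, r=0 | Power, r=.385 |
|---|---|---|---|
| 0 (no switch) | .380 | 73% | 80% |
| .25 | .285 | 47% | 54% |
| .50 | .190 | 23% | 26.5% |
| .75 | .095 | 9% | 10% |
| 1 | 0 | 5% | 5% |

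**4. Dilution with metformin half as effective as Avandamet.** Means 0, a, 2a give f = a·√(2/3), so a=.465. Assume that switched women split evenly between the drugs (the protocol gives no split) and catch up fully. Their mean is 1.5a, and f = a/√6 = .19. Power is 23% (r=0) or 26.5% (r=.385), and all of it comes from metformin versus Avandamet. Steps 3 and 4 ignore the extra spread from mixing two drugs in one group.

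**5. The comparison that stays clean.** For metformin versus Avandamet at 20 per arm without covariate, power ≈ Φ(d·√(20/2) − 1.96). The gap in step 4, d=.465, gives Φ(−0.49) = 31%. If metformin is three quarters as effective (d=.223), the result is Φ(−1.25) ≈ 10%.

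**The case against.** The strongest reply is that the 1-year endpoint serves the objective in Study Endpoints/Objectives, which compares the two drugs. That comparison is randomised and intact at month 12. This stands, and it limits the point: the 1-year endpoint fails the diet-alone part of the objective, not all of it. It does not remove the point, because Objective and Overview includes diet alone and the sample size is for three groups.

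Four stronger readings are tempting, and the documents do not support them.

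- *No placebo-controlled insulin comparison is planned.* One is: the curves are scheduled at 6 months, and Statistical Plan compares groups then. What it lacks is a rank as primary or secondary.
- *Any 1-year difference reflects exposure time only.* Step 4 of the working shows otherwise: it can come wholly from metformin versus Avandamet.
- *Phase 3 does not exist.* The text shown leaves it undefined. The protocol mentions an optional surveillance stage, the flow chart is not available here, and the sample-size paragraph calls Phase 1 pre-treatment, so it may use another numbering.
- *The stated 80% power is wrong.* It follows with a correlation of about .385.

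A delayed-start design is also legitimate when its 1-year contrast is defined as early against late start. This protocol does not define it so.

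**Conclusion.** The point holds and should be corrected before the primary analysis is fixed. The protocol sets a 1-year primary outcome, empties the diet-alone arm at 6 months, and sizes a three-group comparison without saying in which month it is made. The primary analysis as written cannot compare either drug with diet alone.

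That conclusion rests on the text alone. The size of the power loss does not: it depends on the assumed catch-up, the assumed correlation and the relative effect of the two drugs. With equal drugs and catch-up from a quarter to full, power runs from 47% down to 5% against a reference of 73%, or from 54% down to 5% against 80%. These figures illustrate the loss and are not forecasts.

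**What to change.** - In Study Endpoints/Objectives and in Outcome Parameters / Analytical Endpoints, make the primary endpoint the change from baseline to month 6 (end of Phase 1) in fasting and 1-hour insulin, compared across the three arms as randomised.
- Make the 12-month change secondary: compare the two arms randomised to active drug from the start, and report the switched women separately and descriptively.
- In Summary of sample size calculations, replace Phase 3 with the month meant, and confirm that f=.38 is the planning effect at month 6. The paragraph does not tie it to any month, and the only dated preliminary result is the 1-year weight change.

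Two other routes would also remove the contradiction: a 1-year primary comparison limited to the two active arms and sized for that, with 6-month insulin as a named placebo-controlled endpoint; or an explicit early-versus-delayed-start definition of the 1-year contrast. The month-6 route fits the stated three-group objective best.

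Cost: amendment wording and a check of the planning effect. If f=.38 does not hold at 6 months, the sample size must be revisited. No visit is added and the reassignment can stay as planned. The 1-year result loses primary status, but it had no placebo control to lose.

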#### Summary of sample size calculations:

The study design comprises 3 groups in one pre-treatment (Phase 1) and one post-treatment (Phase 3) measurement of outcome. Preliminary data from our open label use of metformin and other randomized clinical trials suggest that metformin affords large treatment effects. Nonetheless, as the large effect may be due in part to placebo, we will structure our sample size to detect more moderate treatment effects. Using an analysis of covariance, a sample size of 60 patients (20 per group) will provide at least 80% power to detect a moderate to large effect size ( $f=.38$ ) for a two-sided test of significance at a critical value of .05. While 20 patients per group are required to meet the anticipated effects, we will target 25 per group to allow for 20% attrition. The proposed attrition rate is less than rates reported in research studies of other medications evaluated for weight reduction, such as sibutramine (32%) and xenical (24%). However, the rate reflects attrition rates from our own preliminary data and from other published studies of patients treated with metformin analyzed using an intention-to-treat or comparable analysis such as studies of obesity in women, and children, PCOS, and HIV-related lipodystrophy.

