#### Statistical Plan

Mean, median, range and distribution of all baseline study variables will be determined (SPSS (13.0); site differences will be assessed using an Analysis of Variance (ANOVA). All primary and secondary outcome variables will be evaluated using an intention-to-treat analysis with a last observation carried forward (LOCF) for missing data, Paired t-tests will be used to calculate baseline changes in insulin parameters, body weight, BMI, cardiovascular risk factors, and related serum markers (adiponectin, leptin, ghrelin, resistin, C-reactive protein and other inflammatory markers, vitamin D and IGF-binding proteins at 6 and 12 months. Non-parametric measures will be used for comparison of group mean changes at 6 and 12 months. Statistical models will be used to calculate the primary (crude, non-adjusted) treatment effect of the respective study arms and for covariate adjustment by age, initial BMI category and menopausal status,

[figure not shown]

|  |                 |
|--|-----------------|
|  | and study site. |
|--|-----------------|

Publication / Presentation Plan:

Following the analysis of baseline data, abstracts will be submitted for presentation at annual meetings, including The Endocrine Society, The ADA, The American College of Cardiology, NAASO (The National Association for The Advancement of the Study of Obesity, NAMS, (The North American Society for Menopause). Publications will be prepared and submitted at regular intervals, following the collation of baseline data, and the completion of each study phase. A final summary manuscript will be submitted within 6 months of the study completion.

Estimated Study Budget/Requested Support (per patient cost, study medication, other supplies):

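### The printed 80% power belongs to a three-group effect that includes placebo, but at the 1-year primary endpoint the only intact contrast is metformin versus Avandamet, for which no power is given

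*Protocol*

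**What the plan says.** The Protocol's Summary of sample size calculations describes the design thus: "The study design comprises 3 groups in one pre-treatment (Phase 1) and one post-treatment (Phase 3) measurement of outcome". It then states that "a sample size of 60 patients (20 per group) will provide at least 80% power to detect a moderate to large effect size", with f = .38, by analysis of covariance, "for a two-sided test of significance at a critical value of .05". The target of 25 per group allows for 20% attrition. The effect size is argued from metformin's effect, scaled down: "as the large effect may be due in part to placebo, we will structure our sample size to detect more moderate treatment effects". The Statistical Analysis Plan row adds that TZD-based studies and comparator trials were also used, but gives no expected difference between metformin and Avandamet.

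The primary outcomes are the 1-year changes in fasting and 1-hour insulin (Study Endpoints/Objectives; Outcome Parameters / Analytical Endpoints). The Study Endpoints/Objectives row says: "The study objective is to compare the effects of metformin, and Avandamet® on markers of insulin resistance". Objective and Overview of the Study also names diet alone as a comparator. After the first six months, "patients in the diet plus placebo group will then be crossed over to one of the two active study arms" (Study Design). The Statistical Plan says: "Statistical models will be used to calculate the primary (crude, non-adjusted) treatment effect of the respective study arms". It calls for intention-to-treat with last observation carried forward.

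**The concern.** The power figure and the primary time point do not fit together. The figure is for the spread of three group means, one of them placebo. When the primary outcome is read at 1 year, nobody is on placebo. The arms that have stayed on one assigned treatment are metformin and Avandamet, which is the pair named in the Study Endpoints/Objectives row. Diet alone is available as randomized only up to 6 months.

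An overall f measures the spread of all the means and does not determine the gap between any chosen two. A good part of the spread behind f = .38 may be the distance from placebo. A reader who takes the 80% as the chance of separating the two drugs at 1 year is relying on a figure that was not calculated for that purpose. The protocol itself fixes the sample size, effect size, time point and crossover, so this is not a detail left to an analysis plan.

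**Working it through.** **Inputs from the protocol.** N = 60, 20 per group; f = .38; two-sided α = .05; three groups; analysis of covariance; 25 per group randomized.

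**Assumptions, because the protocol is silent.** The pattern of the three means, and the baseline–outcome correlation r. The base case takes f as already on the analysed (residual) scale.

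**Step 1. The printed figure.** For the overall test, λ = N·f² = 60 × 0.1444 = 8.66. The noncentral F with 2 and 56 df gives power 72.9% (73.0% with 2 and 57 df, no covariate). This is not 80%; in equal groups, N = 72 would be needed. The printed figure is reached only with an input that is not stated:
- r of about 0.385: λ = 8.664/(1 − 0.385²) = 10.17, power 80.0%.
- A test with 1 numerator df: 82.5%.
- All 75 randomized women analysed: λ = 10.83, power 83.0%.

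The attrition step does reproduce: 60/(1 − 0.20) = 75.

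**Step 2. From f to the gap between the two drugs.** f is the SD of the group means divided by the residual SD.
- Equally spaced means (placebo, metformin, Avandamet) with step s: f = s·√(2/3), so s = .38/0.8165 = 0.465 SD.
- Metformin equal to placebo, Avandamet apart by d: f = d·√2/3, so d = .38/0.4714 = 0.806 SD. A search over all patterns in which placebo does worst confirms this as the largest gap between the drugs.
- Placebo midway between the drugs: gap = 2 × 0.465 = 0.931 SD.

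**Step 3. Power for the pair.** Two-sample noncentral t with noncentrality d·√(n/2) and 2n − 2 df. In the last column d is divided by √(1 − 0.5²) = 0.866, with 37 df.

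| Pattern | Gap (SD) | 20 per arm | 25 per arm | 20 per arm, assumed r = 0.5 |
|---|---|---|---|---|
| Equally spaced | 0.465 | 30.0% | 36.4% | 38.0% |
| Metformin = placebo | 0.806 | 70.0% | 79.7% | 81.8% |
| Placebo midway | 0.931 | 81.8% | 89.7% | 91.1% |

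With r = 0.385, the value that brings the overall test to 80%, the first two rows give 34% and 77% at 20 per arm. If the two drugs are equal and both differ from placebo, the gap is zero and the rejection rate is 5%, although f is still .38.

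**Step 4. What 20 per arm can detect.** Solving the same formula for 80% power at n = 20 gives d = 0.91 SD. To reach 80% at the gaps above would take about 74 per arm for 0.465 SD and 26 per arm for 0.806 SD.

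**The case against.** Several points on the other side stand in whole or in part.

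- **The primary contrast is inferred.** The protocol never attaches its 80% to a drug-versus-drug test, and one statement of the objective includes diet alone. This is true. The contrast follows from the 1-year endpoint, the 6-month reassignment and the Study Endpoints/Objectives row taken together.
- **The analysis set may be larger.** Under intention-to-treat with last observation carried forward, 25 per arm would be analysed, and the case with metformin equal to placebo rises to about 80%. This stands, so 70% is not an unconditional ceiling. It assumes that carried-forward values show the same effect, although the 12-month insulin curves are planned only for study completers.
- **Everyone is on one of the two drugs at 1 year.** If the reassigned women split evenly (not stated) and were pooled with the original arms, 30 versus 30 would give 43% with equally spaced means and 87% with metformin equal to placebo; f = .38 read as a two-group effect (0.76 SD) would give 82.5%. The protocol does not rule this out, but its 20 per group does not describe it, and it mixes 12 months of drug with 6.
- **The basis of f is wider than metformin against placebo.** TZD-based studies are cited as well. That is so, but f = .38 is derived from no stated figure.

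A reader might infer that the trial has only 30% power, or that a null drug comparison is the likely result under the plan's own effect size. The documents do not support either: equal spacing is my assumption, and other patterns with the same f give 70% or 82%. Nor does any text plan to read a non-significant difference as similarity of the drugs.

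**Conclusion.** The point holds in a conditional form. The only stated power is for a three-group effect that includes placebo, while the 1-year primary outcome leaves metformin versus Avandamet as the one contrast of arms still on a single assigned treatment. The protocol gives neither an expected difference nor a power for that pair, and f = .38 does not supply one.

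At 20 per arm, with f on the residual scale, power is about 30% for equally spaced means and at most about 70% if placebo does worst; about 82% requires placebo to lie midway between the drugs. Analysing 25 per arm, or assuming a baseline correlation of 0.5, lifts the 70% to about 80% or 82% but leaves the equally spaced case at 36% to 38%. Separately, the overall test has about 73%, not 80%, on the stated inputs, so tying the existing figure to that test does not by itself make it right.

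**What to change.** In Summary of sample size calculations:

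1. State that the existing figure refers to the overall three-group test. Correct it to about 73% at N = 60 and f = .38, or state and justify the baseline correlation (about 0.385) that would give 80%.
2. Name the 1-year contrast and give what it can detect. For example: *For metformin versus Avandamet at 1 year, 20 per arm give 80% power only for a difference of about 0.91 residual SD. At f = .38, assuming equally spaced arm means (0.47 SD apart), power is about 30%.* If 25 per arm are to be analysed, give the corresponding figures.
3. State that this contrast is reported as an estimate with a 95% confidence interval.

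The change is to protocol wording only. It needs no extra patients, and its cost is a less favourable stated power.

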|--------------------------------------------------------------------------------------------------------|--------------------------------------------------------------------------------------------------------------------------------------------------------------------------------------------------------------------------------------------------------------------------------------------------------------------------------------------------------------------------------------------------------------------------------------------------------------------------------------------------------------------------------------------------------------------------------------------------------------------------------------------------------------------------------------|
| Number of Patients                                                                                     | Total enrollment 75-85 (approx. 20 per site) to capture 60 patients completing the study                                                                                                                                                                                                                                                                                                                                                                                                                                                                                                                                                                                             |
| Projected Enrollment Timeline (proposed start date, proposed finish date, anticipated enrollment rate) | 
Please see attached timeline
 
Projected start date: Sept 1, 2006
 
Projected study completion date: August 30, 2008 (without optional phase)
 
Time-table assumptions:
 
The investigators anticipate a rapid study start-up phase due to:
 
 
a. general ease of enrollment of obesity studies
 
b. investigators' access to large and diverse patient populations in their individual practices and the community
 
c. availability of field tested patient education materials and study instruments
 
d. the availability of nursing and nutrition staff with broad
 
 |

[figure not shown]

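### The stated power of at least 80% for 60 patients at f = .38 cannot be reproduced from the protocol's inputs; the conventional three-group F test gives 73%

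*Protocol*

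**What the plan says.** The Protocol, under Summary of sample size calculations, describes the design this way: "The study design comprises 3 groups in one pre-treatment (Phase 1) and one post-treatment (Phase 3) measurement of outcome". Using analysis of covariance, it states that "a sample size of 60 patients (20 per group) will provide at least 80% power to detect a moderate to large effect size", with f given as .38, "for a two-sided test of significance at a critical value of .05". It then inflates for dropout: "we will target 25 per group to allow for 20% attrition".

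The paragraph does not say whether f is scaled to the unadjusted or the covariate-adjusted SD. It gives no correlation between covariate and outcome, and it does not say whether the test is the overall three-group comparison or one contrast. The Statistical Plan lists age, BMI category, menopausal status and site as adjustment covariates and calls the primary treatment effect unadjusted.

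On enrolment, the Number of Patients row reads "Total enrollment 75-85 (approx. 20 per site) to capture 60 patients completing the study", and the Study Design row says "an initial study population of 75 women from 3 clinical sites will be randomized".

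**The concern.** The sample size paragraph appears to supply everything a standard power calculation needs: number of groups, group size, effect size, significance level and method. Putting those values into the usual formula gives a figure about 7 points below the one stated.

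This sentence is the only quantified justification for 20 completers per group. If the conventional reading is the intended one, the planned effect would be missed 27% of the time, about a third more often than the 20% a reader would take from the text.

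**Working it through.** **Inputs** (all from Summary of sample size calculations): k = 3 groups, N = 60 (20 per group), f = .38, two-sided alpha = .05, analysis of covariance.

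**1. Try to reproduce the stated figure.** The overall test is an F test with k − 1 = 2 numerator df and N − k − c denominator df, where c is the number of covariates. With f on the residual SD the noncentrality is λ = N·f² = 60 × .38² = 60 × .1444 = 8.664. Power is the probability that a noncentral F exceeds the 5% critical value.

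| Covariates | df | Power |
|---|---|---|
| 0 | 2, 57 | 73.0% |
| 1 | 2, 56 | 72.9% |
| 6 | 2, 53 | 72.7% |

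A simulation of the no-covariate case (100,000 runs) gave 72.8%. Rounding of f does not close the gap: .375 gives 71.7% and .385 gives 74.1%. A chi-square approximation gives 75.4%. The stated 80% is not reproduced.

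**2. What 80% would take on this reading.**
- At N = 60: f = .41 (.4115 to .4117, depending on the covariate count).
- At f = .38: 69 women give 79.5%, 70 give 80.1%, and 72 (the first equal split, 24 per group) give 81.3%.
- At f = .38 with all 75 randomised women measured: 83.0%.

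**3. Readings that reach 80% with 60 women at alpha .05.** Each needs something the protocol does not state. The correlations are assumptions, shown as a range.

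(a) f on the unadjusted SD. A covariate with correlation ρ to the outcome shrinks the SD by √(1 − ρ²), so the effective f is .38/√(1 − ρ²). With one covariate (df 2, 56):

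| ρ | Power |
|---|---|
| .2 | 74.8% |
| .3 | 77.2% |
| .385 | 80.0% |
| .4 | 80.6% |
| .5 | 85.1% |
| .6 | 90.4% |

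(b) A 1-df two-sided test with the same λ = 8.664: 82.5%.

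(c) A repeated-measures between-group test on the average of the two measurements, λ = 60 × .1444 × 2/(1 + ρ): 80.1% at ρ = .7.

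**4. Attrition.** 60/(1 − .20) = 75, or 25 per group. This step is correct.

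**5. Site count.** The Study Population section refers to four study centers; the Objective and the Study Design row give three. 4 × 20 = 80 lies within 75-85; 3 × 20 = 60 does not.

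**The case against.** The strongest reply is that 73% is in effect the analysis-of-variance figure, with no credit for the covariate, whereas the protocol names analysis of covariance with a pre- and a post-treatment measurement. If f was set on the unadjusted SD, a baseline correlation of about .39 is enough for 80%. The reference to a two-sided test also fits a single contrast at least as well as an overall F test, and that contrast has 82.5%. Nor does the Statistical Plan's unadjusted primary effect settle the matter. The endpoint is already a change from baseline, and for an unadjusted change score with f on the raw SD, λ = 8.664/[2(1 − ρ)], which gives 73% at ρ = .5 and 83% at ρ = .6. All of this stands, and it is why the point is that the figure cannot be reproduced, not that it is certainly false.

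The analysis is also planned as intention-to-treat with last observation carried forward, so 60 completers need not be the analysis set. That stands too. It does not support the stated sentence, which attaches its power to 60. The 83% at N = 75 assumes measured outcomes; carried-forward values may dilute the effect.

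Two stronger readings are tempting and should be resisted.
- A reader might infer that power is lower still for each pairwise comparison. That depends on the pattern of means. With 20 against 20, drug versus placebo has d = .38 × 3/√2 = .81 and 70% power if both active arms are equal. If metformin lies midway, the extreme pair has d = .38 × √6 = .93 and 82%.
- A reader might infer from the per-site figure that only 60 women would be randomised, leaving 48 after attrition. The protocol has no such scenario: it fixes the total at 75 or more, and 20 per site fits four centers.

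**Conclusion.** The claim of at least 80% power does not follow from the inputs stated beside it. On the conventional reading (2-df F test, f on the residual SD), power is 73% and type II risk 27%. The shortfall is about 7 points, equivalent to needing f of about .41 instead of .38, or about 72 analysed women instead of 60.

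It would be too strong to say that any three-group analysis of covariance of this size has 73% power, because the unstated SD scale, correlation or contrast could bring the figure to 80% or above. The protocol does not let the reader choose between these. The attrition inflation is sound, and the planned enrolment of 75 is enough for 83% on the conventional reading if outcomes are measured in all. The differing number of sites is a minor inconsistency that does not affect the power result.

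**What to change.** In Summary of sample size calculations, do one of the following.
- Restate the power: 60 completers (20 per group) give 73% for f = .38 and 80% for f of about .41; 75 randomised women with measured outcomes give 83% for f = .38.
- If another basis was intended, state the SD on which f is scaled, the assumed covariate-outcome correlation and its source, and the test (overall or a named contrast), and give the power that follows from them.

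As a minor tidy-up, reconcile the number of sites (four in The Study Population, three in the Objective and the Study Design row) with the approximate 20 per site in the Number of Patients row.

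The cost is protocol wording and, on the first option, a slightly less favourable stated power. No extra enrolment is asked for.
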